### Sample size

The sample size is estimated for linear mixed effects modeling with two conditions, three repeated measures, and clustered data. Based on a pilot study among caregivers in a care center, means and standard deviations can be estimated for empathy, self-efficacy, and knowledge. The desired power is set to a minimum of 0.90 and α = .05. The three care centers are taken into account as clusters with intra cluster correlation of .2. We estimate that around 90 participants are needed to detect a main effect of 0.5 SD on the primary outcome measures. To correct for attrition, we increased the highest number by 10%, bringing the total number of participants to 100 parents/relatives and 100 professional caregivers.

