### Recruitment

The study will include two samples. The participants will be 100 professional caregivers and 100 parents/relatives of adults with mild or moderate ID (intelligence quotient (IQ) 35–70). This also included persons with ID and additional psychiatric diagnoses such as autism spectrum disorders, or additional physical disabilities such as a visual impairment. The group of professional caregivers will be recruited within three Dutch centers providing care for persons with ID living in group homes. Each care center has multiple group homes and activity centers in The Netherlands. The group of parents/relatives of adults with mild or moderate ID will be recruited from these and other centers throughout The Netherlands. Close relatives, such as a brother, sister, uncle, or aunt, can participate if the parents of a client are no longer the primary caregivers.

Participants in both samples will be recruited and enrolled by the participating care centers, which combined are connected to 3107 professional caregivers and 4830 parents/relatives. Participants will be invited to participate when they care for one or more persons with mild or moderate ID.

Candidates will be excluded from participation when they primarily care for persons with severe intellectual disability (IQ below 35) or when their use of HiSense APP-ID will be interrupted for more than five consecutive days. For parents/relatives, only one family member per client is included.

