### Randomization

Cluster randomization among locations of the care centers will be used to prevent crossover effects between professionals and parents/relatives. Group homes and activity centers will be randomly assigned to the treatment condition or the care-as-usual condition by an independent party, based on order of entry and a pre-determined order of treatment conditions. Randomization of participants will occur after enrollment but before the baseline assessment. Participants are to be informed of their allocated condition shortly after T0 to reduce any response bias during the baseline assessment.

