### Procedure

Participants will be recruited by the participating care centers. First, the centers will acquire groups of professional caregivers who work together in group homes or activity centers for persons with mild or moderate ID. Next, parents/relatives of clients will be approached for participation. If needed, recruitment for parents/relatives can be extended to other group homes and other care centers. All participants will be asked to give active consent for participation.

The study will contain three time points of data collection (Fig. 2): before the start of the intervention (T0), at the end of the intervention (40 days after T0), and 30 days after T1. For professional caregivers, researchers will make an appointment at the residence and provide a laptop to complete the questionnaires. Family members can come to the care center or complete the questionnaires online at home. Each measurement will take 45 min.

After T0, participants in the intervention condition will be asked to use the HiSense APP-ID for a total of 30 days. Each day, participants will complete four multiple-choice questions, which takes a maximum of 5 min per day. They will receive feedback on their original answer (correct or wrong) and an additional explanation for the correct answer. Participants do not have to log in on weekends, but after 2 days of inactivity, they are reminded of their participation by an automatic email. If a participant has not been active for 5 days, that person is excluded from further participation. There are 120 questions in total, which should be completed within 40 days. At the end of day 10 and day 20, participants can revisit the questions that were answered incorrectly. Participants in the “waiting list condition” receive care as usual.

At 40 days after T0, the knowledge tests and questionnaires are completed again by participants in both conditions (T1, see Fig. 1). After a retention period of 30 days, the questionnaires are completed for the last time (T2). Participants in the care-as-usual condition are then encouraged to use the app.

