### Data analysis

All statistical analyses will be conducted using SPSS version 23 [46]. Both groups of participants (parents/relatives and professionals) will be treated as separate groups in the analyses because we expect that matching will not be possible. Partial intention-to-treat analyses will be performed: participants will be excluded from the analysis if fewer than two data points are available. All other participants will be analyzed according to their assigned condition.

For social validity, empathy, and self-efficacy, average item scores will be reported for each questionnaire. For the knowledge test, the total number of correct answers is to be used. Reliability statistics (Cronbach’s alpha) will be reported for the knowledge test at T0, T1, and T2.

Descriptive statistics will summarize the characteristics of the participants. Demographic variables are recorded as categorical variables, so chi-square analyses will be used to determine whether there are statistical differences between participant groups in the experimental and control condition at T0.

Increases in knowledge, empathy, and self-efficacy will be assessed using linear mixed effects modeling. Condition will be entered as a fixed effect and intercepts for participant and care center as random effects. Demographic variables will be included as a covariate in the analysis if significant between-group differences are found at T0.

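### The model omits the randomised unit: group homes and activity centers are allocated, but random intercepts are given only for participant and care center

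*Protocol article*

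**What the plan says.** Four sections of the protocol article bear on this.

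- **Randomization** makes the location the unit of allocation: "Cluster randomization among locations of the care centers will be used to prevent crossover effects between professionals and parents/relatives", and "Group homes and activity centers will be randomly assigned to the treatment condition or the care-as-usual condition by an independent party".
- **Recruitment** and **Procedure** show that a location can contribute several participants. On structure: "Each care center has multiple group homes and activity centers in The Netherlands". On the professionals: "the centers will acquire groups of professional caregivers who work together in group homes or activity centers". For the other sample the rule is different: "For parents/relatives, only one family member per client is included". Those participants may also come from other homes and from centers beyond the three.
- **Sample size** places the clustering at a higher level: "The three care centers are taken into account as clusters with intra cluster correlation of .2". No ICC is given for locations.
- **Data analysis** states the model: "Condition will be entered as a fixed effect and intercepts for participant and care center as random effects". No section adds group home or activity center to it.

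**The concern.** In a cluster-randomised trial the condition effect is a comparison between clusters. Its standard error must therefore contain the variance between clusters. Colleagues in one home share clients, management, training and one allocation, so their scores are likely to be correlated. A participant intercept handles repeated measures on one person. It does nothing for correlation between colleagues.

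The care-center intercept does not fill the gap. Locations are allocated, and each center has several, so condition can vary within a center. Center then acts as a block: it removes differences between centers and leaves differences between locations of the same center untreated. A variance estimated from only three centers is also very imprecise.

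At stake is the primary comparison in the professional trial. Standard errors that are too small could let chance differences between homes pass as an effect of the app on knowledge, empathy or self-efficacy.

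**Working it through.** **Inputs from the article.** α = .05 (two-sided assumed; sidedness is not stated), power 0.90, effect 0.5 SD, three measurements, about 90 participants per sample before attrition and 100 after, three care centers with ICC .2.

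**Inputs not given, so assumed.** Participants per location, m = 3 to 10. Location-level ICC, .05 to .2; the article's .2 belongs to care centers. Correlation between repeated measurements, .6 in the simulation.

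**1. The article's own figure.** One measurement per person needs 2 × ((1.960 + 1.282)/0.5)² = 84.06, so 85 per arm or 170 in total. Averaging three measurements with correlation ρ multiplies 84.06 by (1 + 2ρ)/3.

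- ρ = .3: 84.06 × 1.6/3 = 44.8, so 45 per arm, 90 in total.
- ρ = .5 with a further factor (1 − .2) for comparison within centers: 84.06 × 2/3 × .8 = 44.8, again 90 in total.

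The 90 is thus reachable, but it cannot be confirmed because ρ is not stated. The attrition step reproduces: 90/0.9 = 100. Neither route contains a location term.

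**2. Type I error when location is ignored.** The design effect is DE = 1 + (m − 1) × ICC. A nominal 5% test then has actual level 2 × (1 − Φ(1.96/√DE)).

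| m | ICC | DE | 1.96/√DE | Actual level |
|---|---|---|---|---|
| 3 | .05 | 1.10 | 1.869 | 6.2% |
| 3 | .2 | 1.40 | 1.656 | 9.8% |
| 5 | .05 | 1.20 | 1.789 | 7.4% |
| 5 | .1 | 1.40 | 1.656 | 9.8% |
| 5 | .2 | 1.80 | 1.461 | 14.4% |
| 10 | .05 | 1.45 | 1.628 | 10.4% |
| 10 | .1 | 1.90 | 1.422 | 15.5% |
| 10 | .2 | 2.80 | 1.171 | 24.1% |

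With m = 1, DE = 1 and there is no inflation.

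**3. Simulation of the main effect.** The set-up was 4000 null trials per scenario, about 100 participants, locations spread over three centers, and a center-adjusted test on the mean of T0 to T2 that ignores location. At ICC .05, .1 and .2 the rejection rates were 9.0%, 11.7% and 18.2% for m = 5, and 12.8%, 20.3% and 31.1% for m = 10. These exceed the formula mainly because averaging three measurements shrinks the person-level variance and raises the location share. At ICC .2 and ρ = .6 the ICC of the mean is .2/((1 + 1.2)/3) = .273, so DE = 1 + 4 × .273 = 2.09 for m = 5 and the formula gives 17.5%.

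**4. Simulation of change from baseline.** The test was on the mean of T1 and T2 minus T0. If location effects are constant over time they cancel, and rejection stayed near 5% in every scenario. If 20% of the location variance varies over time, rejection was 6.3% to 10.3% for m = 5 and 7.4% to 16.1% for m = 10 (ICC .05 to .2).

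**5. Information and power.** With m = 5 and ICC .2, 100 participants carry the information of 100/1.8 ≈ 56. If a sample gives power 0.90 without location clustering, a correct analysis has power Φ(3.242/√DE − 1.96). That is 84% at DE = 1.2 and 68% at DE = 1.8, before any loss from having few degrees of freedom.

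**The case against.** **The article condenses a fuller plan.** This carries little weight. The random effects are stated, not left out, and the sample-size section uses the same level.

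**The size is not known.** This stands. A reader might infer that the false-positive rate is two to five times nominal. The article does not support that as a fact, because it gives neither location size nor location ICC. A range of 9.8% to 24.1% arises only if the center-level ICC of .2 is carried over to locations of 3 to 10 participants. At ICC .05 with 5 per location the formula gives 7.4%, about 1.5 times nominal. The assumed correlation also matters. The Empathy section reports test–retest values of .62 to .72 for the Interpersonal Reactivity Index subscales but .97 for the Empathy Quotient. At .97 the simulated excess over the formula nearly disappears.

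**The tested effect may be change.** This stands in part. The hypotheses and the analysis section speak of increases, and a stable location effect cancels from change. However, condition is the only fixed effect named, and the sample size is powered for a main effect, so the main-effect reading is the better supported one.

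**Parents and relatives.** A reader might infer equal inflation in both trials. That goes too far. One person per client and wide recruitment make small clusters probable, and locations with one participant cause no inflation.

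**Both conditions within each center.** This is likely but is nowhere stated. The allocation follows order of entry, and no stratification by center is described.

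**Conclusion.** The omission is certain from the text: the randomised unit is missing from a model that lists its random effects. The direction for the condition main effect is also clear, given positive correlation within locations and more than one participant per location. It rests on condition varying within centers, which is a likely inference.

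The size is conditional. The design-effect figures of about 7% to 14% (5 per location, ICC .05 to .2) and about 24% (10 per location, ICC .2) illustrate what the stated model could produce. They are not estimates for this trial, and they shrink towards 5% for change from baseline with stable location effects. The point applies mainly to the professional trial. It should be corrected before analysis, because the same model serves every primary outcome.

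**What to change.** - **Model.** Add a random intercept for the randomised location, with participant nested in location. Where change over time is tested, consider a location-by-time term as well. Use Satterthwaite degrees of freedom so that the test reflects the number of locations. In a check with 12 to 24 locations, a test on location means kept the level at 4.5% to 5.4%.
- **Center, professional trial.** Enter care center as a fixed effect with three levels.
- **Center, parent/relative trial.** Use a center term that allows for centers beyond the three; a three-level factor would not fit the recruitment rules. Participants who are alone at their location form clusters of one.
- **Data.** Record a pseudonymous location code. The Data recording section describes identification numbers assigned at the care centers but mentions no location code, and without one the model cannot be fitted. Everyone at a location shares one allocation, so the code must be held in a way that does not reveal condition to the blinded research team.
- **Sample size.** Restate power with location as the cluster, giving the assumed location size and ICC.

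The cost is a changed model statement, one extra variable and some care over its handling. Confidence intervals will be wider, and effective power will be lower than the stated 0.90.

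### The model meant to assess increases contains no increase term, and with ordinary residuals its participant intercept assumes equal correlations across unevenly spaced visits

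*Protocol article*

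**What the plan says.** In the Protocol article, Data analysis, the aim is "Increases in knowledge, empathy, and self-efficacy will be assessed using linear mixed effects modeling". The terms of that model are then given in one sentence: "Condition will be entered as a fixed effect and intercepts for participant and care center as random effects". Demographic covariates may be added if the arms differ at T0. "All statistical analyses will be conducted using SPSS version 23". No visit term, condition-by-visit term, random slope or residual covariance structure is named.

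Under Procedure, data are collected "before the start of the intervention (T0), at the end of the intervention (40 days after T0), and 30 days after T1". Under Study design, T2 is described as a retention measurement. Under Measures, the knowledge test uses new questions at each visit.

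Under Sample size, "The sample size is estimated for linear mixed effects modeling with two conditions, three repeated measures, and clustered data", and the target is an overall effect: "We estimate that around 90 participants are needed to detect a main effect of 0.5 SD on the primary outcome measures".

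**The concern.** There are two linked problems in the one sentence that lists the model.

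First, an increase is a difference between visits, and its treatment effect is a condition-by-visit contrast. With condition as the only fixed effect, the coefficient is the arm difference averaged over T0, T1 and T2. That average includes the baseline visit, at which the app cannot yet have acted.

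Second, once the visit terms are added, as the stated aim requires, the standard errors of the between-visit contrasts depend on the within-person covariance. The participant intercept is the only within-person term named. With independent, equal-variance residuals it gives compound symmetry: equal variances at T0, T1 and T2 and equal correlations for all pairs. Measurements 70 days apart may well correlate less than measurements 30 days apart, and a knowledge test with changing questions need not have a constant variance. If the correlations differ, the model uses their average for every contrast, and the T0–T2 test can reject too often.

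**Working it through.** **The plan's own figure.** For 0.5 SD, power 0.90 and two-sided α = .05 (sidedness is not stated), the plain two-sample size is 2 × (1.960 + 1.282)² / 0.5² ≈ 84.1. That is 85 per arm, or 170 in total. The stated figure of about 90 is reached only with a within-person correlation ρ that the article does not give:

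- mean of three visits, ρ = .3: 170 × (1 + 2 × .3)/3 = 90.7;
- the same with a factor (1 − .2) for the care-center correlation, ρ = .5: 170 × .8 × (1 + 2 × .5)/3 = 90.7;
- mean of T1 and T2 adjusted for T0, ρ = .4: 170 × [(1 + .4)/2 − .4²] = 91.8.

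So the figure can be neither confirmed nor refuted, and it does not reveal which contrast or covariance was assumed. The step from 90 to 100 does reproduce (90/0.9 = 100).

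**Inputs for the check.** Two arms of 45 (90 analysed, 1:1, assumed), complete data, free means for each arm and visit, and equal variances over visits. Gaps of 40, 30 and 70 days come from Procedure. The correlations are assumptions. A care-center intercept that is constant over visits cancels from each person's change, so it is left out.

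**Formula.** For visits j and k with correlation r_jk, the true variance of the between-arm difference in change is 2σ²(1 − r_jk)(1/n₁ + 1/n₂). The random-intercept model with independent residuals uses 2σ²(1 − r̄)(1/n₁ + 1/n₂), where r̄ is the mean of the three correlations. Hence

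model SE / true SE = R = √[(1 − r̄)/(1 − r_jk)], and the large-sample false-positive rate is 2[1 − Φ(1.96 R)].

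**Example: decay by actual days, with .70 at 40 days.** The correlations are .70 (T0–T1), .70^(30/40) = .765 (T1–T2) and .70^(70/40) = .536 (T0–T2), so r̄ = .667. For T0–T2, R = √(.333/.464) = .847, with rate .097. For T0–T1, R = √(.333/.300) = 1.054, with rate .039. For T1–T2, R = √(.333/.235) = 1.191, with rate .020.

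| Assumed pattern | T0–T1: R (rate) | T0–T2: R (rate) | T1–T2: R (rate) |
|---|---|---|---|
| Equal correlations | 1.00 (.050) | 1.00 (.050) | 1.00 (.050) |
| Mild decay: .70, .70, and .65 for T0–T2 | 1.03 (.044) | 0.95 (.062) | 1.03 (.044) |
| First-order serial, ρ = .5 | 1.08 (.034) | 0.88 (.084) | 1.08 (.034) |
| First-order serial, ρ = .7 | 1.11 (.030) | 0.85 (.095) | 1.11 (.030) |
| First-order serial, ρ = .9 | 1.14 (.025) | 0.83 (.105) | 1.14 (.025) |
| By days, .70 at 40 days | 1.05 (.039) | 0.85 (.097) | 1.19 (.020) |

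**Simulation (40,000 trials per scenario, 45 per arm).** Under serial correlation with ρ = .7, the random-intercept model rejected at .028 for T0–T1 and .094 for T0–T2. Under true compound symmetry it rejected at .051 for both. Under another assumed pattern (T0–T1 .62, T1–T2 .72, T0–T2 .55) it gave .054 for T0–T1, .077 for T0–T2 and .025 for T1–T2. Giving each contrast its own variance, as an unstructured covariance does, returned .051 for all three. With equal correlations of .65, both methods held 5%.

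**Averaged contrast.** With complete data, the arm difference averaged over all visits depends only on the variance of each person's mean. The random-intercept model estimates that variance correctly, so this contrast is unaffected.

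**The case against.** The strongest reply is that the article does not fix the residuals. Naming a participant intercept does not make the residuals independent with equal variance, because a mixed model can hold both an intercept and a structured residual. That detail is commonly left to a fuller plan, which is not shown. This stands. A reader might infer that the plan forces compound symmetry; the text supports only that this follows under ordinary residuals.

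A second reply is that the trial is sized for a main effect, and an effect averaged over visits is immune with complete data. This also stands, but it does not dispose of the point. The stated aim is increases, T2 exists to measure retention, and participants with only two of the three visits stay in the analysis, so complete data are not assured.

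Two further inferences are tempting and unsupported:

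- **That the article's own reliability figures show decay.** The IRI test–retest range of .62–.72 is a spread across subscales. It says nothing about which pairs of visits correlate more.
- **That the app itself makes the standard errors wrong.** Only one arm receives it. If it merely multiplies that arm's variance by 1.5 at 45 per arm, R is 1.00. If it lowers the correlation with baseline in that arm (.5 against .7), the rates are .061 for both increases from T0 and .030 for T1–T2. A pattern of .50/.80/.45 (T0–T1, T1–T2, T0–T2) in the app arm, with a constant .65 in controls, gives .063 (T0–T1), .070 (T0–T2) and .021 (T1–T2). These are modest effects that rest wholly on assumed correlations.

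**Conclusion.** The point holds in a conditional form. The part that needs no assumption is that the listed model contains no term for an increase, although increases are what it is meant to assess.

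The covariance part rests on three assumptions: ordinary independent residuals, between-visit contrasts as the target, and correlations that fall with time. Under these, the T0–T2 test at nominal 5% rejects at about 6% with mild decay and up to about 10% with strong serial decay. T1–T2 is conservative. T0–T1 is near nominal or conservative under pure decay, so it would be wrong to say that all the increase tests are too liberal.

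Under equal variances and correlations there is no error. The uneven gaps and the changing knowledge questions make that equality doubtful, but the documents do not show it to be false. The matter should be settled in the plan before analysis; it does not by itself invalidate the trial.

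**What to change.** Enter visit as a categorical fixed effect together with condition-by-visit, and state which contrast is primary for each outcome. Replace the participant intercept with an unstructured residual covariance over T0, T1 and T2 within participant (SPSS MIXED, REPEATED visit, SUBJECT participant, COVTYPE UN). The intercept becomes redundant once this is in place. Keep the cluster-level random intercepts. Pre-specify a fallback for non-convergence, such as heterogeneous Toeplitz and then heterogeneous compound symmetry. If compound symmetry is to be kept, justify it in the plan.

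The cost is a line or so of syntax and the matching wording, plus four more covariance parameters (six instead of two). About 90 participants at three fixed visits can support these. There is a small risk of non-convergence, which the fallback covers. If the correlations really are equal, almost nothing is lost.

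### Professionals' sample: with only three care centers, a fixed center factor is a cheap improvement on the planned random intercept, but it does not by itself secure the 5% level

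*Protocol article*

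**What the plan says.** The Data analysis section of the protocol article assesses the three primary constructs with linear mixed models, separately for professionals and for parents/relatives. Condition is the fixed effect that it names, with "intercepts for participant and care center as random effects".

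The Sample size section makes the center level explicit: "The three care centers are taken into account as clusters with intra cluster correlation of .2". It sizes each sample for a condition main effect: "We estimate that around 90 participants are needed to detect a main effect of 0.5 SD on the primary outcome measures".

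Under Recruitment, the professionals "will be recruited within three Dutch centers providing care for persons with ID". Parents/relatives may also be recruited from other centers in the country, so three levels are certain only for professionals.

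Under Randomization, the units allocated are group homes and activity centers inside the care centers. They are assigned "based on order of entry and a pre-determined order of treatment conditions". Stratification or blocking by care center is not mentioned. These locations do not appear as a term in the described model.

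**The concern.** A variance component for center has to be learned from the spread of three center means. When that estimate comes out too low or at zero, the model in effect drops center. Real differences between centers are then treated as ordinary noise between participants. Condition varies within center, so this does no harm while the arms have the same center mix. If the mix differs by chance, part of the center difference enters the condition effect, and the standard error does not reflect it. The result is a main-effect test that rejects somewhat too often, with confidence intervals slightly too narrow.

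A fixed factor removes center differences whatever their estimated size. The random intercept offers little in return, because three named partner organisations are hardly a sample of centers.

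**Working it through.** **The plan's own figure.** The inputs are "The desired power is set to a minimum of 0.90 and α = .05" (two-sided assumed), an effect of 0.5 SD and three measures. One measurement needs 168.1 participants before rounding (85 per arm, 170 in total). The mean of three measures scales this by (1+2ρ)/3, where ρ is the within-participant correlation. The article does not give ρ, so its figure of about 90 cannot be reproduced uniquely. Two readings match:
- ρ = .3, ignoring center: 168.1 × 1.6/3 = 89.7.
- ρ = .6, with the center share removed: 168.1 × (2.2/3 − .2) = 89.7.

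The attrition step holds: 90/.9 = 100, or 90 × 1.1 = 99.

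**How well three centers determine a variance.** With 2 df, the 95% interval for the between-center mean square runs from 2/χ²(.975; 2) = 0.27 to 2/χ²(.025; 2) = 39.5 times its estimate.

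**How often the estimate is zero.** This happens when the between-center mean square falls below the within-center one. Take 100 participants in three equal centers, about 33.3 each:
- One outcome, ICC .2: the expected ratio is 1 + 33.3 × .2/.8 = 9.33. P(F with 2 and 97 df < 1/9.33 = .107) = 10.1%.
- Mean of three measures, ρ = .6: the within-center variance is 2.2/3 − .2 = .533. The ratio is 1 + 33.3 × .2/.533 = 13.5, and P(F < .074) = 7.1%.

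Simulation agrees: 10–12% on the first scale (estimates at or close to zero) and 7–10% on the second.

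**Effect on the condition test.** Simulated under the null with 96–100 participants, three centers, center ICC .2, half the locations allocated to each arm without regard to center, and no location variance. The number of locations is assumed because the article gives none.

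| Trials per setting | Locations | Random center | Fixed center |
|---|---|---|---|
| 20,000 | 12 / 16 / 20 | 6.1 / 5.7 / 5.6% | 4.9 / 5.0 / 5.1% |
| 8,000 | 12 / 16 / 20 | 6.6 / 5.5 / 5.5% | 5.3 / 4.5 / 5.0% |
| 5,000 | 12 / 20 | 6.1 / 5.9% | 4.9 / 5.2% |
| 4,000–6,000 (mean of three measures) | 10–30 | 4.9–6.2% with Satterthwaite df, 5.2–6.5% with z | 4.7–5.6% |

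Monte Carlo standard errors are about 0.16, 0.25 and 0.31 points for the first three rows.

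- In the first row, the SD of the estimate is .208 / .200 / .193 (random) against .208 / .199 / .192 (fixed), so precision is the same.
- In the trials of that row with a center variance near zero, the random version rejects 9.4 / 9.0 / 6.7%.
- Power at 0.5 SD (mean of three measures) is 89.0% random and 88.6% fixed with 20 locations, and 84.0% and 82.3% with 10. The random version's small advantage comes with its higher type I error.

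**What happens when locations carry variance.** Center is switched from random to fixed, and location stays out of the model:
- Location ICC .05, one outcome: 11.6% falls only to 10.2% (12 locations), and 8.0% to 7.4% (20).
- Location variance .05 or .10, mean of three measures: fixed center still rejects 15.1% or 24.2% (10 locations) and 10.2% or 14.7% (20).

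With location means as the unit of analysis, the level is nearly right and the choice for center still shows: 5.9% random against 5.2% fixed (12 locations), 5.8% against 5.4% (20).

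**When the difference vanishes.** With arms balanced within centers, the random version rejects 4.7–5.1%. With centers entering one after another on an alternating list, the figures are 4.7% random and 4.6% fixed (12 locations), and 5.2% for both (20).

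**The case against.** The strongest case against is that this is a side issue resting on unstated details.

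- **The missing location term matters far more.** This stands in full. A reader might infer from the first table that changing one term restores the 5% level for the model as described. The documents do not support that: the randomized unit is the location, and the model leaves it out.
- **Imbalance by center is inferred from silence.** This also stands. The article gives an order-of-entry list and does not say whether it is blocked or stratified; a fuller protocol may. The excess is therefore conditional.
- **The planned test may be a change over time.** The hypotheses speak of increases, and a condition-by-time contrast is unaffected by a center intercept in complete data. The model description names only condition, and the sample size targets a main effect, so the concern applies to that test. A reader might conclude that the intervals for every primary outcome are too narrow; that is not established.
- **Parents/relatives may come from more than three centers.** This stands. With eight centers, a fixed factor lost precision (SD .190 against .179), so the point should not be carried over to that sample automatically.
- **The effect is small, and a random center matches the sample-size assumption.** True. With Satterthwaite degrees of freedom the two ranges overlap, and nothing in the plan contradicts itself here. The direction is nevertheless the same in the simulations without balance by center at ICC .2, and it persists when location means are analysed.

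**Conclusion.** The point holds as a small, inexpensive improvement for the professionals' sample. With three centers and the plan's correlation of .2, the random intercept makes the condition main-effect test about 0.5 to 1.5 points too liberal, and a fixed factor removes that contribution at equal precision. This rests on four assumptions: about 100 participants, 12 to 20 locations, allocation not balanced by center, and a main-effect test.

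It is no cure for the analysis as a whole. With an assumed location variance of .05–.10, type I error stays at about 7–24% whichever way center is entered, until location is modelled too.

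**What to change.** In the Data analysis section, for professionals, enter care center as a three-level fixed factor beside condition, and keep random intercepts for participant and for the randomized location (group home or activity center). The location term should be part of the same change, since the center factor alone leaves the larger problem in place. For parents/relatives, use the fixed factor only if recruitment stays within the three centers; if many centers contribute, a random center intercept may be kept.

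The center change costs one line of wording and one term in the SPSS syntax. Its statistical price arises only if centers differ much less than the plan assumes. At a true center ICC of .02–.05 the standard error grows by about 4–8% with 12 locations and 2–3% with 20.
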